### Phase III: Developing post-CS home care guide

#### Objective

To explore expert opinion on the content of post-CS home care guide prepared through the review of literature, and the opinions of post-CS mothers and nurse midwives

*Design*. Participatory Action Research (PAR) will be applied to the development of a post-CS home care guide [38]. The findings from the integrative review (phase I) and qualitative study (phase II) will be used to prepare a draft of the post-CS home care guide (prototype 1). The draft guide will be reviewed by maternal and child health experts for appropriateness and adequacy of the post-CS home care guide.

A one-day workshop will be conducted to validate prototype 1. Participants in this workshop will be obstetricians and gynaecologists, nurse midwives, nutritionists, health promotion specialists and community health specialists. The participants will be obtained from their professional associations. Three representatives will be requested from each of the Association of Obstetrics and gynaecology (AGOTA), Tanzania Midwives Association (TAMA), Food and Nutrition Association of Tanzania (FONATA) and Public Health Association (TPHA). Further, the Ministry of Health, Community Development, Gender, Elderly and Children (MHCDGEC) will also be requested to provide three representatives making a total of 15 participants. During the workshop, the prototype 1 home care guide will be presented by the first author (MM) section by section and the process that led to the formation of the guide will be also shared. The aim is to present how the authors came up with the prototype I of the guide. Thereafter, three (3) focus group discussions will be conducted where each group will be led by a moderator and another person will take notes.

Each group will be composed of one member from each speciality. Participants in each group will discuss the draft guide and give recommendations on each component and content of the guide (prototype 1). The participants will discuss each section separately. They will start with the first section and give their opinion and recommendations before moving to the following section. They will do so using a discussion guide until the entire draft of the home care guide is discussed. They will be requested to give reasons for recommending or not recommending the items within the guide. Then they will present the recommendations in a plenary where consensus will be reached [39]. In the end, the participants will be asked for any additional comments or opinions on previous sub-sections to wrap up the session. Prototype 1 will then be revised based on the ground recommendations to form prototype 2.

### Pre-testing the prototype II post-CS home care guide and tool

The prototype II of the post-CS home care guide will be pretested with nurse-midwives and post-CS mothers in the post-natal ward by the researcher, to assess the feasibility and applicability of the guide in a real clinical setting. Also, the pre-test will involve the assessment of the tool that will be developed based on the designed home care guide; on its ability to measure knowledge of home care after hospital discharge for both nurse midwives and post-CS mothers. The pre-test will employ a pre-and post-interventional assessment for both nurses and midwives. The pre-test study will take place in the Morogoro region, in Morogoro regional referral hospital (MRRH).

A convenient sample of post-natal mothers will be obtained based on their availability during the data collection period and provided written consent to participate in the study. Thereafter, mothers will be trained by a researcher using the developed post-caesarean home-based guidelines (prototype II). However, before the intervention, participants will be assessed for their baseline knowledge about home care after CS. During the intervention, various training strategies will be used including lecturing and lecture discussion. Following the intervention, post-natal mothers will be asked to return to the facility after 7 days after CS for post-training interventional assessment. In each visit to the post-natal clinic, mothers will be requested to provide feedback and suggestions on the adequacy of the education content, clarity of the information, and applicability of the recommendations in their homes, and to provide additional information that could be included in the care of mothers at home after caesarean section deliveries (if any).

The post-caesarean home-based guidelines (prototype II) will then be used to train nurse midwives after pre-assessment of knowledge on post-CS home care is conducted. The training intervention will involve 50 purposive recruited nurse midwives (i.e., 20% of the total sample size of nurse midwives in phase 4) [40] who are working in maternity wards at MRRH for at least one year; in the meeting room through lecturing method and slide projection. The aim is to familiarise the nurse midwives or midwives with the prototype II post-CS home care guide. Post-test to nurse midwives will be done on the same day after pretesting and intervention. The nurse midwives will then be required to teach post-CS mothers about home care before discharge as per the guideline to ensure its integration into the healthcare system and sustainability.

The pre-interventional knowledge assessment will be compared to the post-interventional knowledge assessment to evaluate change in knowledge before and after the intervention. Not only that but also nurse midwives will also be required to grade items of the guide by using the Likert scale (very important, important and less important); at the end of the pre-test study (phase 3), it is estimated that there will be recommendations on each item of the guide. They will also be required to give suggestions on the adequacy of the guide, clarity of the item, the applicability of the guide in hospital settings and proper timing of counselling post-CS mothers.

#### Analysis

In this study, data will be analysed by using the Statistical Product for Service Solutions (SPSS) software programme version 25.0. Before conducting the analysis, error checking (data cleaning) will be performed by using Frequency Distribution Tables to ensure the completeness and accuracy of data.

Descriptive analysis will be used to analyse participants’ characteristics to determine the frequencies and percentages of their distribution. Descriptive statistical analysis will also be used to establish frequencies and percentages of the Likert scale responses among nurse midwives at the end of the pre-test study to determine the prevalence of their recommendations in each item. Knowledge of the participants will be categorised into two responses, adequate if the participants score above the mean of the knowledge question and inadequate knowledge if the participants score below the mean [41]. Logistic regression will be used to determine the association between the predictor variables such as age, education level, marital status, gravidity and parity and participants’ knowledge about home care after CS set at a confidence interval of 95% with a margin of error of 5%. The baseline and end-line timepoints will be used to establish the effect of the intervention on knowledge.

The results from the pre-test study will help to improve the guide and to form the post-CS section home care guide (prototype 3), which will be used in phase IV of the study.

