#### Sample estimation

*Sample size for nurse midwives*. The sample size for the intervention and control group of nurse midwives will be obtained by using the formula for comparing two independent samples (intervention group vs control group), guided by the study by Joho [40]. In her study, which is conducted in 39 primary health facilities in Dodoma, she found that the knowledge proportion of nurses on the timing of administration of uterotonic before and after the educational intervention was 44.8% and 63.4%, respectively [40,43].

$$n=2\{Z_{\alpha }\sqrt{[\pi_{0}}(1‐\pi_{0})]+Z_{\beta }\sqrt{[\pi_{1}}(1‐\pi_{1})]\}/{\left(\pi_{1‐}\pi_{0}\right)}^{2}$$

n = Minimum sample size

Zα = Standard normal deviation of 1.96 at 95% confidence interval (CI).

Zβ = Standard normal deviation 0.80 with the power demonstrating statistically significant difference before (baseline) and after intervention between two groups at 80%.

p0 = Proportion of an intervention group at baseline = 44.8% (0.448)

p1 = Proportion after the intervention = 63.4% (0.634)

With a 5% attrition rate:

$$n=2\{1.96\sqrt{\left[0.634(1-0.634)\right]}+0.8\sqrt{\left[0.448(1-0.448)]\right\}}/{\left(0.634‐0.448\right)}^{2})$$

n = 78

So, the minimum sample size will be 78 plus a 5% attrition rate = 82

The ratio of the intervention group to the control group will be 1:2. Therefore, the sample size for the control group will be 164.

Thus, the total sample size in this study will be 246 nurse midwives.

*Sample size for post-CS mothers*. The sample size for the intervention and control group of post-CS mothers will be obtained by using the following formula;

The formula for comparing two independent samples (intervention group vs. control group), and using the proportion of SSI for pre-intervention was 16% and 4.9% for post-intervention [44]. A prospective observational cohort study involving active in-patient and post-discharge surveillance cohort study was done in DRRH at Obstetrics and Gynaecology Department where [43];

$$n=2\{Z_{\alpha }\sqrt{[\pi_{0}}(1‐\pi_{0})]+Z_{\beta }\sqrt{[\pi_{1}}(1‐\pi_{1})]\}/{\left(\pi_{1}‐\pi_{0}\right)}^{2}$$

n = Minimum sample size

Zα = Standard normal deviation of 1.96 at 95% confidence interval (CI).

Zβ = Standard normal deviation 0.8 with the power demonstrating statistically significant difference before (baseline) and after intervention between two groups at 80%.

p0 = Proportion of an intervention group at baseline = 16% (0.16)

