#### Dependent variables. Knowledge of post-CS home care

Participants who will score at least 75% of the maximum score will be regarded as possessing adequate knowledge of home care after CS, otherwise inadequate knowledge [47].

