### Analysis of knowledge of home care after CS

The outcome variable is dichotomised (1 = adequate knowledge; 0 = inadequate knowledge), and so a generalised estimating equation (GEE) will be employed to assess the impact of the intervention on knowledge, whereby odds ratio, confidence interval and p-value will be presented. GEE is an extension of the ordinary logistic regression model for correlated/repeated measure data. In this case, it seems to be more appropriate as will be having more than one measurement/observation of each subject at different time points.

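### The phase III pre-test calls knowledge adequate relative to an unnamed sample mean, so the measured gain depends on an unstated choice and the 75% cut-off used in phase 4 is never tried out

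*Protocol article*

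**What the plan says.** **Phase III.** The section on pre-testing prototype II of the guide says that the tool's ability to measure knowledge will be assessed, and that "The pre-interventional knowledge assessment will be compared to the post-interventional knowledge assessment to evaluate change in knowledge before and after the intervention". For the nurse midwives, "The training intervention will involve 50 purposive recruited nurse midwives". The Analysis subsection that follows classes knowledge as "adequate if the participants score above the mean of the knowledge question and inadequate knowledge if the participants score below the mean". It then names a logistic regression of knowledge on participant characteristics and ends: "The baseline and end-line timepoints will be used to establish the effect of the intervention on knowledge". It describes no other knowledge measure.

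**Phase 4.** Under Dependent variables the rule is different: "Participants who will score at least 75% of the maximum score will be regarded as possessing adequate knowledge of home care after CS". The analysis section for knowledge follows from it: "The outcome variable is dichotomised (1 = adequate knowledge; 0 = inadequate knowledge), and so a generalised estimating equation (GEE) will be employed". Under Sample estimation, the nurse midwife numbers rest on two proportions, 44.8% before and 63.4% after an educational intervention in a cited study.

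**The concern.** A cut-off taken from the sample is not a fixed standard. If it is recalculated when the sample improves, it moves up with the sample and hides the improvement. The text does not say whether the mean is that of the baseline, of the end-line, of each occasion separately or of both together. It also leaves a score exactly equal to the mean unclassified, whereas the phase 4 rule (at least 75%) classifies everyone.

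The two phases also use one word for two things. The pre-test feeds prototype 3 of the guide and is meant to check the tool. As written, it would not show whether almost nobody, or almost everybody, reaches 75% of the maximum, and the phase 4 binary outcome depends on exactly that.

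**Working it through.** **1. Which mean is used: closed form.** The article gives no score distribution, so I assume a normal score with SD 15 points and the same SD before and after. For a gain of g points, the share above the cut is:

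- own mean at each occasion: Φ(0) = 50% before and after;
- baseline mean: Φ(0) = 50% before, Φ(g/15) after;
- pooled mean: Φ(−g/30) before, Φ(g/30) after.

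| Cut | g = 5 | g = 10 | g = 20 |
|---|---|---|---|
| Own mean | 50% → 50% | 50% → 50% | 50% → 50% |
| Baseline mean | 50% → 63% | 50% → 75% | 50% → 91% |
| Pooled mean | 43% → 57% | 37% → 63% | 25% → 75% |

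**2. The same check with a discrete score.** Simulation of 50 people, as planned for the nurse midwives, with 20 right/wrong items (assumed), person ability varying on the logit scale with SD 0.8 (assumed), and 10,000 samples:

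| True mean score | Own mean | Baseline mean | Pooled mean |
|---|---|---|---|
| 46% → 46% | 49% → 49% | 49% → 49% | 49% → 49% |
| 46% → 63% | 49% → 53% | 49% → 81% | 34% → 69% |
| 46% → 77% | 49% → 57% | 49% → 96% | 23% → 84% |

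The small rise in the own-mean column comes from skewness as scores approach the maximum. It is not a usable measure of the gain.

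**3. Phase III against phase 4.** Take a sample whose mean is 46% of the maximum. A participant scoring 60% is adequate under the phase III rule and inadequate under the phase 4 rule. The two shares cannot be compared, and the first does not predict the second.

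**4. Phase 4: the plan's own figure.** The printed formula gives 2{1.96√(0.634 × 0.366) + 0.8√(0.448 × 0.552)}/0.186² = 2(0.944 + 0.398)/0.0346 = 77.6, which reproduces the stated 78. With 5% added this is 82, and 1:2 gives 164 controls. Phase 4 is therefore sized on proportions, consistently with a binary outcome.

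**5. Phase 4: what dichotomising costs.** For a small shift in location, the information kept is f(c)² × SD²/[p(1 − p)], where f is the density of the score at the cut and p the share on one side. At the two planned proportions:

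- Normal: 0.3956²/0.2473 = 0.633 at 44.8% and 0.3762²/0.2320 = 0.610 at 63.4%. The loss is 37% and 39%. The best case, a 50% split, keeps 2/π = 0.637.
- Logistic: p(1 − p)π²/3 = 0.814 and 0.763. The loss is 19% and 24%.
- Uniform: (1/12)/[p(1 − p)] = 0.337 and 0.359. The loss is 66% and 64% (67% at an even split).
- Laplace: 2 min(p, 1 − p)²/[p(1 − p)] = 1.62 and 1.15. There is no loss.

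Around these splits the range is thus from none to about 67%. A lopsided split can cost more: at 90% adequate, the loss is 66% (normal), 70% (logistic) and 78% (Laplace), but only 7% (uniform).

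**The case against.** **The rule does not necessarily hide a gain.** A reader might infer that a mean split can never show a change. The article does not support that. It never says that the mean is recalculated, and with a baseline or pooled mean the gain is plain. This stands: the defect is an unspecified cut.

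**The mean split may not be the before-after measure.** In the Analysis subsection it is followed directly by the logistic regression on participant characteristics, where a near-even split does no harm. The promised comparison of assessments could be made on scores. That reading is compatible with the text, but the subsection names no score analysis and closes by using both time points to establish the effect, so the plan should say so.

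**The pre-test has other inputs.** Mothers' feedback, nurse midwives' grading of each item, and suggestions on clarity and timing also shape the revision, and stored scores can be re-cut at 75% later. This stands and limits the harm: knowledge change is one input among several.

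**The phase 4 cut-off is legitimate.** It is fixed in advance, can show change and agrees with the sample size. This stands. A reader might infer that dichotomising is an error that leaves the nurse comparison badly underpowered. For the planned proportions, a standard two-proportion calculation gives 79.2% power at 82 and 164, or 77.1% at 78 and 156, against the stated 80%. The shortfall is small.

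One could also set these figures beside a far higher power for the numeric score. Converting the proportions to a normal shift of 0.473 SD gives, at 78 and 156:

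- adjusted for baseline, Φ(0.473/√[(1 − ρ²)(1/78 + 1/156)] − 1.96) = 95-98% for assumed ρ of 0.3 to 0.5;
- group-by-time, with 2(1 − ρ) in place of (1 − ρ²), 82-93%.

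I would not rely on that contrast. The 44.8% and 63.4% describe knowledge of one item, the timing of a uterotonic, in another study. They are not pass rates on this tool. The baseline-adjusted figure also presumes groups that are balanced at baseline, which a non-equivalent two-hospital design does not ensure.

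**Conclusion.** The point holds for phase III. The rule leaves the cut undefined, and the choice matters: for one assumed 10-point gain with SD 15, the share adequate rises by 0, 25 or 26 percentage points depending on which mean is used. The pattern is the same with a 20-item score. The exact sizes rest on the assumed distributions, but the dependence on the choice does not. Phases III and 4 also define adequate knowledge differently, so the pre-test does not examine the threshold on which the phase 4 outcome is built.

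For phase 4 there is no error to correct. Analysing only the category gives up information: about 37-39% under normal scores with equal SDs, and from none to about 67% under the other shapes tried near the planned splits. Because the article gives no score distribution, no single figure can be claimed.

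**What to change.** **Phase III.** Make the before-after comparison on the numeric score with a paired test, and report the mean change with its confidence interval. Where a category is needed, replace the mean split by the phase 4 rule (at least 75% of the maximum), and report the share reaching it before and after training.

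**Phase 4.** Keep the GEE on the 75% category as planned. Add one analysis of the numeric score that uses baseline: either follow-up score regressed on group and baseline score, or a linear model with a group-by-time term. Name one in advance, because the two can disagree when the hospitals differ at baseline.

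**Cost.** The change is to the text plus one extra analysis. The scores have to be collected anyway in order to be classified, and keeping the binary outcome leaves the sample-size basis unchanged. There are two small downsides. A mean score difference is less familiar to clinicians than the percentage adequate, which is still reported. And if few pre-test participants reach 75%, the phase III logistic regression will have a small group on one side; that is itself useful to know before phase 4.

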### Phase 4: Implementation and effectiveness assessment of post-CS home care guide

#### Objectives

1. To assess the implementation process of post-CS home care guide in preventing SSI among mothers delivered by CS in health facilities in central Tanzania.

2. To evaluate the effectiveness of a post-CS home care guide in the prevention of SSI among post-CS mothers delivered at health facilities in central Tanzania.

3. To evaluate the effectiveness of a post-CS home care guide in improving knowledge of home care after hospital discharge among nurse midwives and post-CS mothers at health facilities in central Tanzania.

### Methodology

#### Study design

Quasi-experimental study design with the non-equivalent control group (pre-and post-test with a control group) will be conducted [42]. The design will involve a baseline assessment of knowledge of post-CS and nurse midwives on home care after hospital discharge both in the intervention and control groups [42]. The intervention group will be exposed to a post-CS home care guide and education for both post-CS mothers and nurse midwives, respectively. In contrast, the nurse midwives and post-CS mothers in the control group will not be exposed to the post-CS home care guide and education but they will receive the usual care offered in their facility.

#### Setting

This phase will be conducted in Dodoma and Singida. In Dodoma, the study will be conducted in Dodoma Regional Referral Hospital (DRRH), where an intervention group (nurse midwives and post-CS mothers) will be obtained. The DRRH provides both Basic Emergency Obstetrics and Newborn Care (BEmONC) and Comprehensive Emergency Obstetrics and Newborn Care (CEmONC) services. It has a separate maternity block for providing maternal and child health services. DRRH will be purposively selected as an interventional hospital because of the recently reported high rate of SSI due to CS [19]. In 2020, DRRH had 9016 total deliveries and the rate of CS was 28.7% (anecdotal evidence).

In Singida, the study will take place at Singida Regional Referral Hospital (SRRH). In SRRH, the control group will be obtained. The SRRH matches with DRRH in the sense that both are referral hospitals in the central zone of Tanzania where most of the complicated cases are managed. Both hospitals provide CEmONC including CS, and they have separate maternity blocks. In 2020, SRRH had a total of 3656 deliveries with a CS rate of 33.5% (anecdotal evidence).

#### Study population

The study will include registered nurse midwives and post-CS mothers. In addition, post-caesarean mothers in post-natal wards will be retained to participate in the study before discharge. The exclusion criteria will be:

Post-CS mothers with prolonged hospitalisation due to maternal or neonatal complications.Post-CS mothers who didn’t receive pre-antibiotic medication prior to surgery, have an infection of amniotic fluid.Mothers whose CS were not performed in the study site (DRRH and SRRH).

Post-CS mothers in the intervention group will be matched based on their age, gravidity, type of CS and their obstetric history such as the previous mode of delivery. Also, nurse midwives will be matched based on their education level and working experience in a maternity unit.

#### Sample estimation

*Sample size for nurse midwives*. The sample size for the intervention and control group of nurse midwives will be obtained by using the formula for comparing two independent samples (intervention group vs control group), guided by the study by Joho [40]. In her study, which is conducted in 39 primary health facilities in Dodoma, she found that the knowledge proportion of nurses on the timing of administration of uterotonic before and after the educational intervention was 44.8% and 63.4%, respectively [40,43].

$$n=2\{Z_{\alpha }\sqrt{[\pi_{0}}(1‐\pi_{0})]+Z_{\beta }\sqrt{[\pi_{1}}(1‐\pi_{1})]\}/{\left(\pi_{1‐}\pi_{0}\right)}^{2}$$

n = Minimum sample size

Zα = Standard normal deviation of 1.96 at 95% confidence interval (CI).

Zβ = Standard normal deviation 0.80 with the power demonstrating statistically significant difference before (baseline) and after intervention between two groups at 80%.

p0 = Proportion of an intervention group at baseline = 44.8% (0.448)

p1 = Proportion after the intervention = 63.4% (0.634)

With a 5% attrition rate:

$$n=2\{1.96\sqrt{\left[0.634(1-0.634)\right]}+0.8\sqrt{\left[0.448(1-0.448)]\right\}}/{\left(0.634‐0.448\right)}^{2})$$

n = 78

So, the minimum sample size will be 78 plus a 5% attrition rate = 82

The ratio of the intervention group to the control group will be 1:2. Therefore, the sample size for the control group will be 164.

Thus, the total sample size in this study will be 246 nurse midwives.

*Sample size for post-CS mothers*. The sample size for the intervention and control group of post-CS mothers will be obtained by using the following formula;

The formula for comparing two independent samples (intervention group vs. control group), and using the proportion of SSI for pre-intervention was 16% and 4.9% for post-intervention [44]. A prospective observational cohort study involving active in-patient and post-discharge surveillance cohort study was done in DRRH at Obstetrics and Gynaecology Department where [43];

$$n=2\{Z_{\alpha }\sqrt{[\pi_{0}}(1‐\pi_{0})]+Z_{\beta }\sqrt{[\pi_{1}}(1‐\pi_{1})]\}/{\left(\pi_{1}‐\pi_{0}\right)}^{2}$$

n = Minimum sample size

Zα = Standard normal deviation of 1.96 at 95% confidence interval (CI).

Zβ = Standard normal deviation 0.8 with the power demonstrating statistically significant difference before (baseline) and after intervention between two groups at 80%.

p0 = Proportion of an intervention group at baseline = 16% (0.16)

p1 = Proportion after the intervention = 4.9% (0.049)

With a 5% attrition rate:

$$n=2\{1.96\sqrt{\left[0.16(1-0.16)\right]}+0.8\sqrt{\left[0.049(1-0.049)]\right\}}/{\left(0.16‐0.049\right)}^{2}$$

n = 145 plus 5% attrition rate 152

So, the minimum sample size is 145 plus a 5% attrition rate = 152

The ratio of the intervention group to the control group will be 1:2. Therefore, the control group sample size will be 304.

Therefore, the total sample size in this [40] study will be 456 post-CS mothers.

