### Analysis of SSI

Binary logistic regression analysis will be used to assess factors associated with SSI.

The general logistic regression model is given as:

$$\log it[\pi (x)]=\log(\frac{\pi (x)}{1-\pi (x)})=\beta_{0}+\beta_{1}x_{1}+\ldots \ldots +\beta_{p}x_{p}$$

Where *π*(*x*) is the SSI status, *x*_*i*_’*s* is set of independent variables and *β*_*i*_’*s* is their respective parameters.

The power of the study will be set at 80% (0.8) while a confidence interval of 95% with a margin of error of 5% (0.05) was used as a statistical measure of significance (< 0.05 was regarded as significant while > 0.05 not significant).

The effect of intervention between groups will be assessed using difference in difference (DID) analysis.

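### Both sample sizes come from an unsquared, equal-group formula, so the planned 1:2 groups do not have the stated 80% power: about 77–79% for nurse-midwives and about 95% for mothers

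*Protocol article*

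**What the plan says.** All of this is in the protocol article. Under Sample estimation, one formula serves both populations. It is n = 2{Zα√[π0(1−π0)] + Zβ√[π1(1−π1)]}/(π1−π0)², with no square on the bracket. The constants are given as "Zα = Standard normal deviation of 1.96 at 95% confidence interval (CI" and "Zβ = Standard normal deviation 0.80 with the power demonstrating statistically significant difference"; the mothers' calculation repeats the second as 0.8.

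- Nurse-midwives: proportions 0.448 and 0.634. "So, the minimum sample size will be 78 plus a 5% attrition rate = 82". The control group is then set at twice that, 164, for a total of 246.
- Mothers: SSI proportions 0.16 and 0.049. "So, the minimum sample size is 145 plus a 5% attrition rate = 152". Then: "The ratio of the intervention group to the control group will be 1:2. Therefore, the control group sample size will be 304", for a total of 456.

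The section Analysis of SSI repeats the target: "The power of the study will be set at 80% (0.8". The Abstract gives different totals: 248 nurse-midwives and 414 mothers.

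**The concern.** The usual sample-size formula for two proportions squares the sum of the two weighted standard deviations before dividing by the squared difference. Without the square the result is not a sample size for any stated power. The direction of the error depends on whether the bracket is above or below 1, so the two populations can be wrong in opposite directions.

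The factor 2 belongs to an equal-allocation calculation, yet the design is 1:2 and the ratio is applied only after n has been found. Zβ has been given the value of the power itself instead of the normal deviate for that power.

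At stake is whether the 80% stated in two sections is the power of either planned comparison. The formula, constants, inputs and results are all printed, so this is not a matter left to a fuller document.

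**Working it through.** **Inputs (Sample estimation).** Zα = 1.96 and Zβ = 0.8 as printed. Nurse-midwives: p0 = 0.448, p1 = 0.634, difference 0.186, squared 0.034596. Mothers: p0 = 0.16, p1 = 0.049, difference 0.111, squared 0.012321.

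**Step 1: reproduce the plan's figures, bracket unsquared, using its own substitutions.**
- Nurse-midwives: bracket = 1.96·√(0.634×0.366) + 0.8·√(0.448×0.552) = 0.944 + 0.398 = 1.342. n = 2×1.342/0.034596 = 77.6, stated as 78.
- Mothers: bracket = 1.96·√(0.16×0.84) + 0.8·√(0.049×0.951) = 0.719 + 0.173 = 0.891. n = 2×0.891/0.012321 = 144.7, stated as 145.

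Attrition: 78×1.05 = 81.9, stated as 82; 145×1.05 = 152.25, stated as 152.

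**Step 2: same inputs, bracket squared.** Nurse-midwives 104.1, mothers 128.9. Neither matches the plan, so the missing square was in the calculation and is not a typesetting slip. Leaving it out lowers the nurse figure by about 25% (77.6/104.1) and raises the mothers' figure by about 12% (144.7/128.9).

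**Step 3: effect of Zβ alone.** With 0.84 in the unsquared formula, n becomes 78.7 and 146.1, a change of about 1 in each. The nurse substitution also swaps the two proportions relative to the printed formula; the printed order gives 78.6, again a trivial difference.

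**Step 4: power of the planned 1:2 groups.** Pooled two-sided 5% test, p1 in the intervention arm (n), p0 in the control arm (2n), participants independent:

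power = Φ{[|p1−p0| − 1.96·√(p̄(1−p̄)(1/n + 1/2n))] / √(p1(1−p1)/n + p0(1−p0)/2n)}, with p̄ = (p1 + 2p0)/3.

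- Nurse-midwives, 78:156: p̄ = 0.510; (0.186 − 1.96×0.0693)/0.0675 = 0.742; power 77.1%.
- Nurse-midwives, 82:164 (no loss): 79.2%.
- Mothers, 145:290: p̄ = 0.123; (0.111 − 1.96×0.0334)/0.0280 = 1.625; power 94.8%.
- Mothers, 152:304 (no loss): 95.7%.

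**Step 5: sensitivity to the form of test.**

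| Reading | Nurse-midwives | Mothers |
|---|---|---|
| Pooled, 1:2, after loss | 77.1% | 94.8% |
| Unpooled, 1:2, after loss | 78.7% | 97.7% |
| Unpooled, 1:2, no loss | 80.6% | 98.2% |
| Continuity-corrected, 1:2, after loss | 72.6% | 92.5% |
| Pooled, read as 1:1 (78 or 145 per group) | 64.7% | 87.5% |

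No row gives 80% for both populations.

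**Step 6: size needed for 80% power, for reference.** n = [1.96·√(1.5·p̄(1−p̄)) + 0.84·√(p1(1−p1) + p0(1−p0)/2)]²/(p1−p0)² in the smaller arm. Nurse-midwives: (1.200 + 0.501)²/0.034596 = 83.6, so 84:168. Mothers: (0.788 + 0.283)²/0.012321 = 93.2, so 94:188. Both are before attrition.

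**Step 7: the Abstract's totals.** If 414 mothers were split 1:2 (an assumption, since the Abstract gives no split), the groups would be 138:276, with power 93.7%. The 248 nurse-midwives do not divide exactly at 1:2.

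**The case against.** The best defence is that little turns on the error.

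- **Nurse-midwives.** The shortfall is about 1 to 3 points. Under Assessment and training of nurse midwives, trained nurse-midwives are post-tested on the training day, so loss in that arm may be small, and with no loss the pooled figure is 79.2%. An unpooled test with no loss just reaches 80.6%. The 84 needed is only two more than the 82 to be recruited. This stands: a reader might infer a seriously underpowered nurse comparison, and the figures do not support that.
- **Zβ.** The wrong value changes n by about 1. This stands too: it is a misstatement to correct, not a driver of the result.
- **Mothers.** The error is in the safe direction. A reader might infer that the mothers' sample is wasteful and should be cut towards 94:188. The documents do not support that. The design has one hospital per arm with non-equivalent controls, and the SSI analysis is a regression on several factors with a difference-in-difference comparison. The simple formula allows for none of this, so the margin may be needed.
- **Difference-in-difference and the nurse comparison.** A reader might also infer much lower nurse power because the plan names this method. That sentence sits under Analysis of SSI. For knowledge, the protocol names GEE, and it gives no pre/post correlation from which to compute such a power.

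What the defence does not remove is the derivation error. The printed method is wrong, and the mothers' power is about 15 points away from the figure stated.

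**Conclusion.** The point holds as an error of derivation. The main faults are the unsquared bracket and the doubling of the control arm after an equal-group calculation; Zβ = 0.80 is a minor third. The stated 80% should read about 77–79% for nurse-midwives and about 95% for mothers.

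These figures rest on the protocol's own proportions, a pooled two-sided 5% test, 1:2 allocation and independent participants. They do not allow for having one hospital per arm or for the adjusted analysis. The error does not show that either sample is inadequate for this simple comparison: the nurse shortfall is slight and the mothers' sample exceeds what the comparison needs. It does mean that a figure on which the protocol relies in two sections is wrong and should be corrected.

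**What to change.** 1. Settle the totals first: 248 and 414 in the Abstract against 246 and 456 under Sample estimation.
2. Replace the printed formula with the standard two-proportion formula at 1:2 allocation, bracket squared and Zβ = 0.84.
3. Keep the planned sizes and restate their power under Sample estimation and Analysis of SSI: about 77% (78:156, after loss) to 79% (82:164, no loss) for nurse-midwives, and about 95% for mothers. If reconciliation changes the sizes, recompute with the same formula.
4. If the sizes needed for 80% power are shown (84:168 and 94:188 before attrition), label them as reference values for the simple comparison and not as replacement targets.

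The cost is a rewrite of one section plus the matching sentences in Analysis of SSI and the Abstract. Keeping the sizes requires no extra participants; the only loss is that the stated nurse power becomes slightly less favourable.
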